### Outcomes

#### Movement competence

The primary outcome of the RCT is to improve children’s CMS as a result of exposure to a MOGBA program, specifically created for this study. The Dragon Challenge [17] movement assessment protocol will be used to observe and assess the movement competence of children.

#### Physical fitness

A composite secondary outcome of children’s physical fitness will be measured using a standing long jump, plank and height. Standing long jump will be assessed by following the guidance provided in the Assessment of Physical Activity [42] manual. Standing long jump will be scaled by height resulting in a percent of standing height jumped. The plank protocol requires participants to maintain a static prone position with only forearms and toes touching the ground [43]. Participants will be asked to keep their feet together with toes curled under the feet, elbows forearm distance apart, and hands clasped together against the floor mat. Participants will be asked to maintain eye contact with their hands, a neutral spine, and a straight line from head to ankles. The child will be given one 5-s practice trial, during which the examiner will instruct the child to adopt the proper position, followed by a 25-s period of rest. The test will begin when the participant demonstrates the correct position; a stopwatch will be started. Participants will be allowed to deviate from the correct position once and can continue the test if they immediately resume the correct starting position within 3 seconds. The test will be terminated on the second deviation from the correct position or if the participant did not return to the correct position after the first warning; the stopwatch will be stopped and the time taken on the test will be recorded as the test score for the plank. Only one trial of the plank will be allowed.

Height will be measured with participants barefoot and in physical education clothes. Height will be assessed using a Leicester Height Measure (Type Seca; Birmingham, UK; range 14 to 207 cm). Instruments will be calibrated to ensure accurate measures. Additionally, sitting height will be assessed with the participant sitting on the box with his or her back and buttocks to the backboard of the stadiometer, and with his or her head in the Franckfort horizontal plane [44].

#### MVPA and sedentariness

To examine if MOGBA has an in-program effect on the amount of MVPA students are engaged in at school, in-school MVPA will be measured using ActiGraph GT3X+, wGT3X-BT or Axivity AX3 accelerometers worn on the wrist as part of a 5-day in-school protocol at baseline and between weeks 7–9 of the intervention period. Accelerometers will be fitted by the classroom teacher at the beginning of each school day (~9am), with the devices removed at the end of the school day (~3pm). Additionally, to investigate if MOGBA has an effect on MVPA during PE lessons, analysis will be performed for the specific session times (2 x 45–60 minutes) in which physical education (control) or MOGBA (intervention) is undertaken.

Accelerometer data are downloaded in raw format using Actilife Software (version 6.13.3) and processed in R (http://cran.r-project.org/) using the software package GGIR [45]. Data extracted between the first midnight and the last midnight are retained for the analysis. Non-wear time is classified within a 60 min time window if for at least two out of the three axes, the standard deviation was less than 13 mg and the value range is less than 50 mg [46]. Data are reduced by calculating the average gravity-based acceleration units (g) per 1-s epoch, with daily time spent in moderate-to-vigorous physical activity (MVPA) determined using the sum of epochs averaging above 201 mg [47]. The average minutes spent in MVPA per day and average daily wear time is computed using data from each participant’s valid days. A valid day is defined as ≥5h on [48], with participants included in the analysis if they have data for at least 4 valid days [49].

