### Statistical analyses

This trial aims to examine whether MOGBA (a) improves children’s movement competence (Dragon Challenge); (b) increases MVPA during PE lessons (acceleromters), (c) reduces sedentary time both in school and outside of school (accelerometers) (d), improves physical fitness (plank and standing long jump), (e) improves self-perceptions of game and physical competence (Game Play Perception Profile). We hypothesize that children in the MOGBA intervention, compared to those in the control group, will display more favorable changes in these variables identified above.

Statistical analyses of the primary and secondary outcomes will be conducted with linear mixed models using IBM PASW Statistics 25 (SPSS Inc. Chicago, IL) software. Impacts are estimated using an intention-to-treat (ITT) approach, with alpha levels set at p < 0.05. Linear mixed models will be fitted to compare continuous outcomes. Group, time, and group-by-time interaction will be assessed as fixed effects within the model, with covariates of gender and year level also included as fixed effects. The school a student belongs to and the research site will be included as a random intercepts within the model to account for the multi-level nature of the data, and subject (student ID) will be included as a random intercept to model repeated measures at the individual level. Differences of means and 95% confidence intervals (CIs) will be determined using the linear mixed models. If the variables used for secondary outcomes (questionnaires) fail tests of multivariate normality, non-parametric methods will be utilised, or the variables for use in the linear models will be an individual’s factor score from a confirmatory factor analysis of the scales with the appropriate estimator chosen given the non/normal nature of the data.

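### The first-to-last-midnight data window does not fit a 5-day, school-hours accelerometer schedule and, depending on when recording starts and stops, can leave too few days for the 4-valid-day rule

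*Protocol article*

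**What the plan says.** Everything on this point stands in the Protocol article, Outcomes, under MVPA and sedentariness.

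- **Schedule.** In-school MVPA is measured by accelerometers "worn on the wrist as part of a 5-day in-school protocol at baseline and between weeks 7–9 of the intervention period". The classroom teacher puts the devices on at about 9am each school day, and they come off at about 3pm.
- **Data window.** "Data extracted between the first midnight and the last midnight are retained for the analysis".
- **Valid day.** "A valid day is defined as ≥5h on".
- **Inclusion.** Children enter the analysis "with participants included in the analysis if they have data for at least 4 valid days".
- **Lesson outcome.** MVPA is also analysed for the times of the two weekly 45 to 60 minute PE (control) or MOGBA (intervention) sessions.

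The section does not say when recording is switched on before the first fitting or off after the last removal. It also does not say whether the midnights are those of the recorded file or those of the wear period. Under Statistical analyses the article adds: "Impacts are estimated using an intention-to-treat (ITT) approach".

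**The concern.** Trimming to the first and last midnight is natural when a device is worn round the clock, because it removes the partial days at either end. In this schedule every day is a partial day of about 6 hours, so the trimming can remove complete school days. There are only 5 days and the inclusion rule needs 4, so losing one day removes all tolerance for absence or short wear, and losing two makes inclusion impossible.

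At stake are the two accelerometer MVPA aims listed under Trial design: MVPA during PE lessons and MVPA in school. The analysed group could be empty, or could consist only of children with complete attendance and wear. Lessons timetabled on the first or last measurement day could drop out of the lesson analysis. The article also fixes no common recording window across three sites and several device models, so the number of retained days could differ between sites.

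**Working it through.** The article gives no expected number of usable days and no expected exclusion rate, so there is no figure of its own to reproduce.

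**Inputs from the article:** 5 school days; wear from about 9am to about 3pm, so about 6 h; valid day at least 5 h; at least 4 valid days; planned sample about 904 (Sample size calculation), used only for scale.

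**Assumption not in the article:** each retained day is valid with probability p, independently, with p from 0.80 to 0.98.

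**Step 1. School days lying wholly between the first and last midnight**

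| Recording runs | First midnight | Last midnight | Days kept |
|---|---|---|---|
| Mon 9am to Fri 3pm | Tue 00:00 | Fri 00:00 | 3 (Tue, Wed, Thu) |
| Before Mon 00:00 to Fri 3pm | Mon 00:00 or earlier | Fri 00:00 | 4 (Mon to Thu) |
| Mon 9am to after Sat 00:00 | Tue 00:00 | Sat 00:00 or later | 4 (Tue to Fri) |
| Before Mon 00:00 to after Sat 00:00 | Mon 00:00 or earlier | Sat 00:00 or later | 5 |

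A run from Wednesday 9am to the following Tuesday 3pm also keeps 3 (Thu, Fri, Mon).

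**Step 2. Share of children excluded per wave by the 4-day rule**

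- 3 days kept: 4 valid days cannot be reached, so 100% are excluded.
- 4 days kept: excluded = 1 − p⁴.
- 5 days kept: excluded = 1 − (5p⁴(1 − p) + p⁵).

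| p | 3 days kept | 4 days kept | 5 days kept |
|---|---|---|---|
| 0.80 | 100% | 59.0% | 26.3% |
| 0.90 | 100% | 34.4% | 8.1% |
| 0.95 | 100% | 18.5% | 2.3% |
| 0.98 | 100% | 7.8% | 0.4% |

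For p = 0.90: 1 − 0.6561 = 0.344 with 4 days, and 1 − (0.3281 + 0.5905) = 0.081 with 5. Of 904 children, about 0, 593 and 830 would remain with 3, 4 and 5 days kept.

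**Step 3. Lessons lost**

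If the two weekly lessons fall on two different weekdays chosen at random, the chance that both lie in the retained days is C(3,2)/C(5,2) = 3/10 = 30% with 3 days kept, and C(4,2)/C(5,2) = 6/10 = 60% with 4. Real timetables are fixed and not random, so this only illustrates the scale.

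**The case against.** **Recording is not wear.** The 9am and 3pm times are when devices go on and off the wrist. Trimming acts on the recorded file, and a device can record while it is not worn. If sites start the devices before delivering them and download them after collection, all 5 days are kept and the 4-of-5 rule works normally. Start and download times are also details that an article often leaves to the full protocol. This stands. A reader might infer that the plan leaves at most 4 days, or that no child or only a minority can be eligible. The text supports neither as a certainty, because both depend on an unstated recording period.

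**The percentages rest on an assumed p and on independence.** This also stands. If invalid days cluster within children, exclusion with 4 days kept is smaller than 1 − p⁴. In the extreme where a child's days are all valid or all invalid, it is 1 − p whether 4 or 5 days are kept, for example 10% at p = 0.90. The 3-day result does not depend on p.

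**The 4-day rule may not govern the lesson outcome.** It follows directly on the computation of average daily MVPA, while the lesson analysis is introduced separately. A reader might infer that the filter applies to lessons too, but the text does not say so. The point is open and needs one sentence.

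**Intention-to-treat is not breached.** A reader might infer a contradiction with the stated approach. A minimum-wear rule decides whether a measurement is usable and moves no child between arms. The planned mixed model, with a random intercept for student, can also use a child with one valid wave. What remains is possible loss and selection of data.

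**The raw data are kept, so trimming can be undone.** True, and this limits the harm. It does not make the stated rule suitable: when recording extends past midnight at both ends the rule removes no school-day data, and otherwise it removes one or two of the five days.

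**Conclusion.** The point holds in conditional form. As stated, the midnight window, the 5-day school-hours schedule and the 4-valid-day minimum are not reconciled. Unless recording extends past midnight at both ends, either 4 days remain and all must be valid, or 3 remain and no child can qualify. With one end trimmed, the extra exclusion per wave compared with keeping all 5 days runs from about 33 percentage points at p = 0.80 (59.0 − 26.3) to about 7 at p = 0.98 (7.8 − 0.4), under independent days and an assumed validity rate. Loss of first-day or last-day lessons is possible under the same condition.

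Only secondary MVPA outcomes are affected. The primary outcome, movement competence by the Dragon Challenge, is untouched. This is still more than a missing detail: the article states a specific processing rule that is at best redundant for a 9am to 3pm outcome and at worst discards the data needed to meet its own inclusion criterion.

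**What to change.** 1. For in-school MVPA, replace the midnight window with a school-day window, from device on to device off (about 9am to 3pm), on each of the 5 measurement days. Keep the 5 h definition and require 4 of the 5 days.
2. For MVPA during lessons, state that a child is included on the basis of valid wear during the timetabled lesson, whatever the number of valid days in the week.
3. Separately, reconcile the wear schedule with the aims that reach beyond school. Statistical analyses lists sedentary time outside school, and the Abstract lists leisure-time MVPA. Devices removed at about 3pm give no data for either, and the school-day window does not change that.

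Items 1 and 2 cost one processing setting and two sentences, with no new data collection. Because files are downloaded in raw format, they can be applied at processing, and should be fixed before any outcome comparison by arm. Item 3 is a decision about which outcomes the trial measures and cannot be settled by processing alone.

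### The accelerometer wear rules are built for a school day and do not fit the outcome of MVPA in a 45–60 min PE lesson

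*Protocol article*

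**What the plan says.** All the relevant rules are in the protocol article under Outcomes, MVPA and sedentariness.

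- **Wear schedule.** "Accelerometers will be fitted by the classroom teacher at the beginning of each school day (~9am"; the devices come off at about 3pm. Recording is a "5-day in-school protocol at baseline and between weeks 7–9 of the intervention period".
- **Lesson outcome.** For MVPA in PE, "analysis will be performed for the specific session times (2 x 45–60 minutes) in which physical education (control) or MOGBA (intervention) is undertaken". MVPA during PE lessons is aim (b) under both Trial design and Statistical analyses.
- **Non-wear.** "Non-wear time is classified within a 60 min time window if for at least two out of the three axes" the signal stays below an SD limit of 13 mg and a range limit of 50 mg.
- **Scoring.** MVPA is the sum of 1-s epochs averaging above 201 mg.
- **Inclusion.** "A valid day is defined as ≥5h on [48], with participants included in the analysis if they have data for at least 4 valid days".

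The section introduces both outcomes and then gives this single processing sequence. It states no wear criterion for the lesson, no exemption of the lesson outcome from the day-level rules, and no treatment of lesson time when the device was off.

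**The concern.** The rules answer the question of whether a child wore the device for enough of the school day. The lesson outcome needs a different question answered: was the device on during these particular 45–60 minutes? A day-level rule can pass a child who has no lesson data and reject a child whose lessons were fully recorded.

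Two things are at stake. The first is false zeros. A still device adds no epochs above 201 mg, so an unworn lesson that goes undetected looks like a completely inactive one. If removal differs between arms, this biases the comparison. It could differ. By weeks 7–9 intervention lessons are run by university-affiliated facilitators with the MOGBA games, while control lessons follow the teachers' usual content. Baseline is recorded before this contrast exists, so a difference in removal that arose at follow-up would enter the group-by-time term and baseline would not cancel it. The direction is not known.

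The second is lost precision. Children with usable lesson data are excluded because of days that carry no information about the lesson.

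**Working it through.** The plan gives no figure for this point, so there is none to reproduce. The check applies the stated rules to a lesson.

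**Inputs from the section MVPA and sedentariness:** worn from about 9am to 3pm, so about 6 h (360 min); lesson length L = 45–60 min, two sessions; non-wear window 60 min; valid day at 5 h (300 min) or more; at least 4 of 5 valid days.

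**Step 1. Can the window detect an unworn lesson?** I assume that a window is flagged only if it lies wholly inside the off-period, since worn minutes with movement would break the SD and range limits. The off-period must then be at least 60 min.
- Off for 45, 50, 55 or 59 min: never flagged, whatever the window step.
- Off for exactly 60 min: flagged only if it lines up with a window.
- Off for longer (for example a 60 min lesson plus changing): this depends on the window step, which the article does not give.

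| Off-period | 60 min step | 15 min step | 5 min step or finer |
|---|---|---|---|
| 65 min | about 8% of alignments | about 33% | 100% |
| 75 min | 25% | 100% | 100% |

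An unflagged off-period counts as worn and contributes 0 min of MVPA under the scoring rule.

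**Step 2. Does the 5 h rule act as a backstop?** The two cases must be kept apart.
- Removal not detected: computed wear stays near 6 h, and the 5 h rule plays no part.
- Removal detected: wear left = 360 − off-period. At 45 min this is 315 min = 5.25 h, and at 60 min it is 300 min = 5.00 h. Both meet the threshold. At 65 min it is 295 min = 4.92 h, and the day fails.

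So a removal of up to 60 min leaves the day valid in either case, and a child could have the device off for both lessons and still keep five valid days. A detected removal of more than 60 min on both lesson days leaves 5 − 2 = 3 valid days, and the child is excluded from the analysis altogether.

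**Step 3. What does the 4-of-5 rule cost?** Assume independent days, each valid with probability p (an assumed range), and two lessons on different days of the recording week.
- P(at least 4 of 5 valid) = 5p⁴(1 − p) + p⁵
- P(at least 1 of 2 lesson days valid) = 1 − (1 − p)²

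| p | At least 4 of 5 | At least 1 of 2 lesson days | Gap |
|---|---|---|---|
| 0.80 | 0.737 | 0.960 | 22 points |
| 0.85 | 0.835 | 0.978 | 14 points |
| 0.90 | 0.919 | 0.990 | 7 points |

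A child with 4 valid days has at most one invalid day, and so always has a valid lesson day. The gap is therefore exactly the share of children dropped despite a valid lesson day. Valid here means the plan's 5 h rule, which by step 2 does not itself confirm wear in the lesson.

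**Step 4. How large could the false-zero effect be?** If a share f of lessons is unworn and scored zero, mean lesson MVPA is multiplied by (1 − f): a fall of 5–20% for an assumed f of 0.05–0.20. With equal true lesson MVPA of m minutes in both arms, a difference Δf in that share creates a spurious difference of m × Δf. For an assumed m of 15–20 min, this is 0 at Δf = 0, 15 × 0.05 = 0.75 min at the low end of a 5–10 point difference, and 20 × 0.10 = 2.0 min at the high end. None of these inputs is in the article.

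**The case against.** The strongest reply is that the valid-day sentence follows one about average MVPA per day and average daily wear time, so it may never have been meant for lessons. A lesson-level rule could sit in the full protocol or analysis plan, and a condensed article may leave processing detail there. This stands in part: the article does not expressly say that the daily rules govern lesson MVPA. But it does not leave the processing to another document. It specifies the pipeline down to epoch length and axis limits, introduces both outcomes first, and then states one inclusion rule for the analysis. Followed as written, that rule is badly matched to aim (b). If a lesson rule already exists, stating it settles the point.

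A reader might infer that every child whose device was off for a whole lesson is counted as doing zero MVPA. The documents do not support that. Nothing says that unworn time is scored zero; this follows only for removals that go undetected, always those under 60 min and sometimes slightly longer ones. Removals above 60 min can be flagged.

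It is also fair that no lesson-time removal is scheduled, that no removal rate is given, and that every bias figure rests on assumptions, with no difference between arms among the possibilities. Finally, a short stillness test, such as 10–15 min, could class children who are waiting or sitting out as non-wear. Setting their lessons to missing would remove low-MVPA lessons selectively. That objection is sound, and the fix below is shaped by it.

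**Conclusion.** The point holds in a limited form. The stated rules cannot verify wear during a 45–60 min lesson. An unworn lesson shorter than 60 min passes both the non-wear window and the day threshold and can be read as zero MVPA, while the 4-day rule removes children whose lessons were recorded. The first part follows from the article's own times and thresholds, given a still device and a window that must be wholly non-wear. The loss from the 4-day rule is 22, 14 or 7 percentage points at assumed daily validity of 0.80, 0.85 or 0.90 with independent days. The size and direction of any bias between arms are unknown.

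This concerns a named secondary aim. The primary outcome, the Dragon Challenge, is untouched. It is still worth changing, because the remedy is cheap and helps both bias and precision.

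**What to change.** Give lesson MVPA its own inclusion rule, separate from that for in-school MVPA:

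- Log the start and stop of each PE or MOGBA lesson in the recording week, and judge wear over that interval only.
- Class a lesson as unworn when the signal stays within the plan's own SD and range limits across essentially the whole lesson, so that brief inactivity is not removed. Vary this stillness threshold in a sensitivity analysis.
- Set unworn lessons to missing, not zero.
- At each time point, include a child with at least one attended lesson in which the device was worn. Attendance at activity sessions is already registered (Fidelity of intervention); control lessons, and baseline lessons in both arms, need an equivalent class list.
- Do not apply the 4-valid-day rule to this outcome. Keep it for in-school MVPA.

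The cost is a few lines of analysis text, one extra processing step on raw data that are collected anyway, and logged lesson times. Some children will contribute one lesson instead of two. The planned mixed model can use a child with one time point missing.

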#### Game and physical self-perceptions

An individual’s levels of perceived and actual physical competence have differing effects on their levels of motivation in a physical domain. Among children, perceived competence appears to affect motivation towards PA more than actual competence [50], and perceived competence appears to mediate the relationship between actual motor skill competence and PA levels [51, 52].

Children in most countries are exposed to increasing levels of game play and team sports as part of the school curriculum from ages 9–12 years. Given the positive relationship between motor-skill competence [7, 46, 53] and game play competence [7], assessment of changes in perceived physical competence and specific game-play competence appear relevant within an intervention designed to improve both.

The Game play perception profile (GPPP) is used to assess self-perception of perceptual-cognitive related game play among upper elementary school children. The GPPP measures two distinct factors using a four-point scale (Strongly Disagree—Strongly Agree): i) game-play perception–five items reflecting ability across game themes, and ii) game self-perception–four items reflecting abilities in relation to others. The instrument displays acceptable item distribution, item total correlations (>.30) and internal reliability (α = .84 & .85). Change in mean (< 5%) and ICC (.81 & .81) indicate the sub-scales display high levels of test-retest reliability, with face validity (proportion of correctly identified question themes) above 80% for all items and sub-scales. The validity of this measure will be further tested in the recruited cohort using confirmatory factor analysis of the underlying factor structure. Children’s physical self-perception will also be measured using an adaptation of Harter’s physical self-perception scale [54]. Six items are framed as either/or statements using a two-point scale on either side of the statement (Really true for me, sort of true for me).

